## Appendix

### The Boston bowel preparation scale

BBPS was applied to each of the three broad regions of the colon: the right colon (including the cecum and ascending colon), the transverse colon (including the hepatic and splenic flexures), and the left colon (including the descending colon, sigmoid colon, and rectum). The points are assigned as follows:

0 = Unprepared colon segment with mucosa not seen due to solid stool that cannot be cleared.
1 = Portion of mucosa of the colon segment seen, but other areas of the colon segment not well seen due to staining, residual stool and/or opaque liquid.
2 = Minor amount of residual staining, small fragments of stool and/or opaque liquid, but mucosa of colon segment seen well.
3 = Entire mucosa of colon segment seen well with no residual staining, small fragments of stool or opaque liquid.

### Adverse reaction

Adverse reaction associated with bowel preparation and colonoscopy procedures—including nausea, vomiting, abdominal pain, bloating, headache, and dizziness—were prospectively categorized by blinded independent assessors.

1) Transient symptoms requiring no intervention, with preserved procedure tolerability;
2) Symptom-driven procedural pauses (<5 min) without compromising examination completion;
3) Intolerable symptoms necessitating premature procedure termination;

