Transcutaneous electrical acupoint stimulation (TEAS), a non-invasive stimulation therapy that combines the advantages of acupuncture and transcutaneous electrical nerve stimulation, has emerged as a promising therapeutic approach in clinical practice (26). As suggested by previous studies, TEAS has been shown to promote recovery of bowel function through modulation of the brain-gut axis (27–30). Recent clinical studies further demonstrate its therapeutic effects in functional gastrointestinal disorders (e.g., functional dyspepsia and chronic constipation), showing significant symptom relief and motility enhancement, potentially mediated by peripheral nerve activity regulation (30, 31). Additional study has confirmed that by enhancing parasympathetic activity, TEAS facilitates high-amplitude propagated contractions, which are critically required for efficient colonic propulsion (32). These mechanisms provide potential scientific support for TEAS in optimizing bowel preparation quality and alleviating the discomfort associated with the bowel preparation process.

To address the critical gap in evidence regarding TEAS for bowel preparation, we conducted a randomized, placebo-controlled clinical trial. This study hypothesizes that TEAS could optimize the quality of bowel preparation and alleviates bowel preparation-related symptoms, offering a potential adjunct to standard pharmacological regimens.

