#### Colonoscopy

All colonoscopies were conducted with the CF-H290l high-resolution adult video colonoscope (Olympus, Tokyo, Japan) by senior endoscopists (≥5 years experience). The endoscopists were blinded to the study’s hypotheses, objectives and patient randomization. Sedation for the colonoscopy was administered using a combination of alfentanil and propofol.

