#### Secondary outcomes

Defecation parameters

Following TEAS/sham-TEAS interventions, patients documented their defecation parameters in the record sheets, including first defecation time, total defecation frequency, and final stool consistency.

Colonoscope outcomes

The evaluated parameters encompassed four key indicators: insertion time, withdrawal time, cecal intubation rate (CIR), and adenoma detection rate (ADR). The insertion phase was defined as commencing with initial rectal visualization and concluding when the endoscope tip traversed the ileocecal valve into the cecal caput. Withdrawal time represents the duration from cecum to anal canal during meticulous mucosal inspection in screening or diagnostic procedures without therapeutic interventions, with a minimum 6-min benchmark indicating thorough pathological evaluation. CIR, which reflects procedural completeness through comprehensive cecal visualization including anatomical landmarks, must be maintained at ≥95% to ensure examination adequacy. ADR calculated as the percentage of colonoscopies with at least one adenoma identified.

Adverse reaction

Research staff documented all adverse reactions occurring during the bowel preparation process and post-colonoscopy, including nausea, vomiting, abdominal pain, distension, headache, and dizziness (refer to Appendix). The incidence rate of adverse reactions was calculated as (number of cases with adverse reactions)/(total number of cases).

Satisfaction and follow-up colonoscopy

At the conclusion of the treatment period, all participants were surveyed regarding their satisfaction with bowel preparation and their willingness to have a follow-up colonoscopy. The details are presented in Appendix.

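### The adverse-reaction outcome pools preparation symptoms with symptoms after sedated colonoscopy and grades both on an incomplete scale partly tied to the examination, so it cannot isolate the hypothesis that TEAS relieves preparation symptoms.

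*Protocol article*

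**What the plan says.** All references are to the protocol article.

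- **Hypothesis (Introduction).** The trial states two aims in one sentence: "TEAS could optimize the quality of bowel preparation and alleviates bowel preparation-related symptoms". The Discussion returns to the symptom aim, naming bloating and nausea.
- **Outcome (Secondary outcomes, Adverse reaction).** "Research staff documented all adverse reactions occurring during the bowel preparation process and post-colonoscopy". The listed symptoms are nausea, vomiting, abdominal pain, distension, headache and dizziness. The summary is one proportion, patients with a reaction over all patients, with no split by phase.
- **Between the two phases (Colonoscopy).** "Sedation for the colonoscopy was administered using a combination of alfentanil and propofol".
- **Grading (Appendix, Adverse reaction).** One three-level scale covers both phases; its scope is given as "Adverse reaction associated with bowel preparation and colonoscopy procedures". Level 1 is "Transient symptoms requiring no intervention, with preserved procedure tolerability". Level 2 is "Symptom-driven procedural pauses (<5 min) without compromising examination completion". Level 3 is intolerable symptoms that end the procedure early.
- **Analysis (Statistical analysis).** Incidence and severity are compared by chi-square test. Adverse reactions are exploratory, without multiplicity correction, and their p-values are descriptive. The same section uses the Wilcoxon rank-sum test for satisfaction.

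**The concern.** The symptom hypothesis concerns the time when the patient is drinking PEG and receiving stimulation. The outcome also counts symptoms that first appear after an opioid and propofol, several of which (nausea, vomiting, headache, dizziness) are on the same list. A patient who is well during preparation and nauseated in recovery counts the same as one who was nauseated while drinking.

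The severity scale adds a second difficulty. Its upper levels describe pausing or ending a procedure, and level 2 names the examination outright. A troublesome preparation symptom in a patient whose examination then runs normally may have no level that fits.

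At stake is the reading of the tolerability result. A difference, or the absence of one, could not be attributed to bowel preparation, although the Discussion aims to present TEAS as a means of relieving its adverse effects.

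**Working it through.** **The plan's own figure.** The only sample-size calculation is for the primary outcome. For 70% v 85%, two-sided 5%, 90% power, pooled variance under the null and no continuity correction:

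n = [1.960·√(2·0.775·0.225) + 1.282·√(0.70·0.30 + 0.85·0.15)]² / 0.15² = 160.8, so 161 per group.

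161/0.80 = 201.25, so 202 per group. Both figures reproduce and are not in dispute. The protocol gives no expected rate for adverse reactions.

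**Inputs for the illustration.**
- Preparation symptom rate under sham: 37%. This is the gastrointestinal intolerance figure for PEG that the Discussion cites from another trial. Its symptom list differs from this trial's: it includes anal irritation, and headache and dizziness are not named.
- Preparation symptom rate under TEAS: 25%, an assumption, with 22% and 28% as alternatives.
- q, the rate of post-sedation symptoms: 10% to 40%, an assumption. Strictly, q applies to patients without a preparation symptom, since only they can become new cases.
- 202 per group, because the Safety assessment section includes all enrolled patients.

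**Direction 1: TEAS acts only on preparation symptoms.** The pooled rate is 1 − (1 − p)(1 − q). With q equal in both arms, the difference is (p_sham − p_TEAS)(1 − q). For 37% v 25%:

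| q | Sham | TEAS | Difference (points) | Power |
|---|---|---|---|---|
| 0 (preparation only) | 37.0% | 25.0% | 12.0 | 74% |
| 10% | 43.3% | 32.5% | 10.8 | 61% |
| 20% | 49.6% | 40.0% | 9.6 | 49% |
| 30% | 55.9% | 47.5% | 8.4 | 39% |
| 40% | 62.2% | 55.0% | 7.2 | 31% |

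With 22% under TEAS, power is 91% for preparation symptoms alone and 81%, 68%, 56% and 45% at q = 10% to 40%. With 28% it is 49% alone, then 38%, 31%, 24% and 20%.

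**Direction 2: TEAS acts only on post-sedation symptoms.** Take 37% preparation symptoms in both arms and q = 30% under sham, halved to 15% by TEAS.
- Sham: 1 − 0.63·0.70 = 55.9%
- TEAS: 1 − 0.63·0.85 = 46.5%
- Difference: 0.63·0.15 = 9.45 points, with no preparation effect at all.

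This is about the size of the 9.6 points that a true 12-point preparation effect leaves at q = 20%. The pooled rate cannot tell the two situations apart.

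**The scale, event by event.**

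| Event | Level that fits |
|---|---|
| Transient, untreated preparation symptom | 1 |
| Symptom that persists or is treated, with no pause or termination | none |
| Pause under 5 min, examination completed | 2 |
| Pause of 5 min or longer, no termination | none |
| Procedure ended early by symptoms | 3 |

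The second row is not remote: the Safety assessment section itself predefines diarrhoea that is intolerable and needs intervention. If the examination still goes ahead, that event matches no level.

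**The test.** The levels are ordered. A chi-square test on the table gives the same result however the levels are arranged, so it makes no use of the order.

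**The case against.** **Dilution is not established.** A reader might infer that post-sedation events are noise that TEAS is not meant to change, so that a real benefit would be missed. The document does not support this. Rationale for parameter selection and the Discussion both cite an effect of PC6 stimulation on postoperative nausea and vomiting. The bias can therefore run either way. This stands, and the point is limited to the pooled rate being unable to isolate the preparation phase.

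**Most preparation symptoms can perhaps be graded.** A reader might also infer that most of them cannot. Level 1 accepts any transient, untreated preparation symptom, and no severity distribution is given from which to say what most symptoms are. The scale is introduced for both preparation and colonoscopy, so the word procedure in levels 1 and 3 may include preparation. This also stands. What remains is an ambiguity on which two assessors could differ, and the unfilled rows above. The lack of a level for no symptom is not a gap, because such patients are non-cases.

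**The outcome is exploratory.** No confirmatory test or power claim depends on it, so the power figures carry little weight alone. That limits the importance of the point. It does not remove it, because a descriptive estimate must still describe the phase named in the hypothesis.

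**Tolerability is measured elsewhere.** The Appendix has a 0–10 rating of satisfaction with preparation, compared by Wilcoxon test. It is a useful supplement, but it is one global rating whose top anchor refers to the examination, and it does not replace symptom incidence by phase.

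**Chi-square is valid.** It is; the issue is efficiency for ordered data, a minor part of the point.

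**The case report form may already hold onset times.** It is not shown. If it does, the fix is easier, but the outcome as defined is still one pooled rate.

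**Conclusion.** The point holds in limited form. As defined, the adverse-reaction rate cannot test or estimate the stated effect on preparation symptoms, because it merges the periods on either side of sedation. If TEAS leaves later symptoms unchanged, the difference shrinks by (1−q), that is by 10% to 40% for q from 10% to 40%. If TEAS acts on later symptoms, an effect may be wrongly credited to preparation, as in 55.9% v 46.5%. The algebra is general. The percentages rest on a 37% figure from another trial and on assumed TEAS and post-sedation rates, so they show how the outcome behaves and do not forecast its result. If the same patients tend to have symptoms in both phases, q among those without preparation symptoms is lower and the dilution smaller.

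The severity scale is not exhaustive, is ambiguous for preparation symptoms and is analysed without regard to order. The documents support neither the claim that most preparation symptoms are ungradable nor the claim that a true benefit would be missed. The primary outcome and the sample size are unaffected. This should be changed, but it does not threaten the trial's main result.

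**What to change.** 1. **Split by phase.** Record whether each reaction began before or after the start of sedation. Make the rate before sedation, over all randomised patients, the exploratory tolerability outcome. Report later reactions separately as safety. Assign a symptom that spans both phases by its onset.
2. **Replace the scale.** Grade both phases on one exhaustive, ordered severity scale that does not depend on interrupting the examination and that gives every event exactly one level, including symptoms that persist or are treated. Keeping the present scale for the later phase would not work, because a symptom arising after the examination cannot pause or end it. Pauses and terminations can be recorded as separate items.
3. **Use the order.** Compare each patient's worst grade, with no symptom as the lowest category, by the Wilcoxon rank-sum test already planned for satisfaction, or by a proportional-odds model.

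The cost is a timing field on the case report form, a revised grading table, a few words in the analysis section and a second results table. Sample size, visits and the primary outcome do not change. The change should be made before allocation is unblinded. Onset and severity that are not recorded at the time may not be recoverable later, so for patients already enrolled the split may be possible only where the source records give the timing.

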### Patient satisfaction

Overall satisfaction with bowel preparation:

0 = A very poor experience with a very painful process and many adverse effects;
5 = The average level; there are some side effects, but acceptable;
10 = The examination has no adverse effects;

Readiness to undergo follow-up colonoscopy

0 = Great reluctance to undergo the examination again;
5 = If necessary, you reluctantly accept to take that;
10 = Willingness to undergo the examination again if necessary.
